# Alloplastic total temporomandibular joint (TMJ) replacement registry: a protocol for a prospective global multicentre observational cohort study

**DOI:** 10.1136/bmjopen-2025-113558

**Published:** 2026-03-09

**Keywords:** Prospective studies, REGISTRIES, ORAL & MAXILLOFACIAL SURGERY, Facial plastic & reconstructive surgery, Observational Study, Head & neck surgery

## Abstract

**ABSTRACT:**

**Introduction:**

Total alloplastic replacement of the temporomandibular joint (TMJ) is a viable treatment option for severe TMJ disorders (TMDs) unresponsive to conservative approaches, as well as for reconstruction of congenital or acquired TMJ defects. However, clinical data on indications, outcomes, complications and long-term effects remain limited, and no global registry currently exists. This study aims to address this gap by establishing an international registry to collect data from patients undergoing total alloplastic TMJ replacement systematically. The registry will document clinical indications and disease progression, explore relationships between treatments, outcomes and quality of life, identify predictors of favourable outcomes and inform future research.

**Methods and analysis:**

This international, prospective, multicentre, observational registry will enrol approximately 200 patients with TMD requiring total alloplastic TMJ replacement, with follow-up lasting up to 5 years postoperatively. The data collected will include underlying disease, treatment details, functional outcomes, patient-reported outcomes and procedure-related adverse events. The registry will also monitor patients who decline surgery and record their reasons. All treatments will adhere to the standard of care at each participating centre.

**Ethics and dissemination:**

Ethics approval was obtained from the responsible ethics committee (EC) at each participating site prior to TMJ surgery. All patients will be enrolled following an informed consent process approved by the relevant EC. Study results will be disseminated through peer-reviewed publications.

Approving ECs include: Krishnadevaraya College of Dental Sciences and Hospital EC, KCDS/Ethical Comm/54/2022–23; Ethikkommission Nordwest- und Zentralschweiz, 2019–02387; University of Belgrade School of Dental Medicine EC, 36/19; National Videnskabsetisk Komité, 2401881; University of KwaZulu-Natal Biomedical Research EC, BREC/00001592/2020; Etikprövningsmyndigheten, 2019–04477; Ethikkommission Medizinische Hochschule Hannover, 8660_BO_K_2019; Ethik-Kommission an der Medizinischen Fakultät der Universität Leipzig, 080/21-lk; Comité de Ética de la Investigación con Medicamentos Hospital Universitario 12 de Octubre, 19/392; Landesärztekammer Rheinland-Pfalz EC, 2025–18012-andere Forschung/nachberatend; Local Ethical Committee at National Medical and Surgical Centre named after NI Pirogoov, LEC meeting 5; Ethikkommission bei der LMU München, 19–589; Komisja Bioetyczna przy Warmińsko-Mazurskiej Izbie Lekarskiej w Olsztynie, 12/2021; De Medisch Ethische Toetsings Commissie Erasmus MC, MEC-2019–0696 and Comissão Nacional de Ética em Pesquisa, 3.825.711.

**Trial registration number:**

NCT03991728.

STRENGTHS AND LIMITATIONS OF THIS STUDYThis is the first prospective, multicentre international registry for total alloplastic temporomandibular joint (TMJ) replacement with up to 5 years of follow-up (FU).The registry will collect high-quality, prospective data on treatment and outcomes from a large cohort of patients undergoing alloplastic total TMJ replacement, providing broader insights into the underlying disease, treatments and outcomes.A limitation of the study is its observational study design, which precludes direct comparison of treatment outcomes across interventions.The extended FU period (60 months) may result in missing data over time.Differences in treatment protocols and reporting standards across participating centres may affect the consistency, quality and comparability of the collected data.

## Introduction

Temporomandibular joint (TMJ) disorders (TMDs) are a broad group of conditions affecting the TMJ, masticatory muscles and surrounding structures, leading to pain and dysfunction of the jaw and the muscles responsible for jaw movement.^1^ Patients with TMDs often present with symptoms, such as limited mouth opening, facial pain, localised facial swelling, malocclusion and facial disharmony, all of which can be severely debilitating and significantly impair daily life.^2^

TMDs affect individuals of all ages, with peak incidence from adolescence to 60 years, and are more common in women.^3 4^ Prevalence estimates range widely, from 5%–15% in earlier studies^5^,^8^ to 30%–50% in more recent reviews.^34 9^,^11^ This discrepancy likely reflects the complex, multifactorial nature of TMDs and the challenges associated with their diagnosis and classification. In addition, advances in diagnostic methods and the use of broader inclusion criteria have likely contributed to higher prevalence estimates in recent years.^3 12^

The first-line treatment for TMDs is conservative, with approaches including patient education, physical therapy, pharmacologic management, occlusal appliances and biofeedback in cases of chronic conditions, often within an interdisciplinary approach addressing physical and psychological factors.^213^,^17^ However, end-stage conditions—such as post-tumour resections, ankylosis, osteoarthritis or congenital and developmental anomalies—may severely impair mandibular function, requiring total joint replacement with alloplastic components for the condylar head and temporal fossa.^18^,^21^ The primary goals of TMJ replacement are pain relief, improved jaw function, corrected occlusion and facial deformities and improved quality of life (QoL).^2 5 14 15 22^

Although it is one of the most frequently used joints in the body, the TMJ is replaced with alloplastic implants much less frequently than joints such as the hip or knee.^23^ This may be partly attributable to the poor performance of early devices, which were associated with high failure rates, frequent revisions, suboptimal trial design and limited outcome monitoring.^7 20^ In addition, the readability, reliability, content and overall quality of online information on TMDs vary widely, which may further contribute to patients’ reluctance to pursue surgical treatment.^24^ Advances in personalised implant design, materials and biomechanics have made modern TMJ replacements safer and more effective.^1920 25^,^27^ As a result, the use of this treatment has increased, with procedure numbers rising and further growth expected in the coming years.^21^

Despite these advances, high-quality clinical data remain limited.^23 28^ Most published studies—excluding case reports—consist of retrospective series from a few centres, often with limited sample size and a potential risk of conflict of interest.^2229^,^31^ Although reported outcomes are generally positive, key questions regarding patient selection, optimal timing of intervention and whether early replacement is beneficial or should be reserved for specific patient subgroups remain unanswered. The UK has established a national TMJ replacement database,^32^ developed under the auspices of the British Association of TMJ Surgeons, to collect longitudinal outcome data within the UK. This database enables surgeons to compare outcomes with peers and share long-term results. However, no global registry currently exists. This highlights the need for international, multicentre studies to better define indications, outcomes, costs, complications and long-term effects of alloplastic TMJ replacement.

This prospective, multicentre observational registry aims to fill this gap. Beyond increasing data availability, the registry will serve as a structured tool to phenotype patients undergoing alloplastic TMJ replacement by documenting underlying disease, indications, comorbidities and broader clinical context. It will capture real-world variability in surgical techniques, implant selection, perioperative management and rehabilitation strategies across centres. In addition, the registry will capture functional outcomes, patient-reported outcomes (PROs), anticipated and procedure-related adverse events (AEs) and data on patients who decline surgery, allowing exploration of decision-making processes and barriers to treatment.

Collectively, these data will support hypothesis generation, enable stratified analyses and inform future comparative effectiveness research and registry-based trials in this field.

## Methods and analysis

### Study design and setting

This is a prospective, multicentre observational cohort study serving as a registry of patients with severe TMD from any cause, either congenital or acquired, requiring alloplastic total TMJ replacement. Table 1 summarises the sites that are currently included in the study.

**Table 1 T1:** Details of participating sites

Participating site	Country	Region
Oral Rehabilitation Centre, Bangalore	India	Asia
University Hospital Basel, Basel	Switzerland	Europe
Clinic for Maxillofacial Surgery, University of Belgrade, Belgrade	Serbia	Europe
Rigshospitalet, Copenhagen	Denmark	Europe
King Edward VIII Hospital, Durban	South Africa	Africa
Falu Hospital, Falun	Sweden	Europe
University Hospital Leipzig, Leipzig	Germany	Europe
Skåne University Hospital, Lund	Sweden	Europe
12 de Octubre University Hospital, Madrid	Spain	Europe
Medizinische Hochschule Hannover, Hannover	Germany	Europe
Pirogov National Medical and Surgical Center (NMSC), Moscow	Russia	Europe
Ludwig Maximilian University Hospital, Munich	Germany	Europe
Wojewódzki Specjalistyczny Szpital Dziecięcy, Olsztyn	Poland	Europe
Erasmus University Medical Center, Rotterdam	The Netherlands	Europe
Karolinska University Hospital, Stockholm	Sweden	Europe
A Beneficência Portuguesa de São Paulo, São Paulo	Brazil	South America
Uppsala University Hospital, Upphsala	Sweden	Europe
Universitätsmedizin Mainz, Mainz	Germany	Europe

### Objectives

The study seeks to broaden understanding of TMDs, treatment patterns and patient outcomes, with a focus on clinical indications, regional variations and patient-reported, clinical and functional outcomes in patients undergoing alloplastic TMJ replacement. Additionally, the study aims to identify predictive factors for favourable outcomes (such as pain reduction, range of motion, occlusal status and QoL) and understand why some patients refuse TMJ replacement.

### Study procedures

In this study, patients will receive treatment based on the local standard of care, with all intervention and postoperative care performed according to the standard procedures at participating sites, as determined by the treating surgeon. The study protocol will not influence clinical decision-making, materials or surgical/imaging techniques, except for the collection of standardised data in a customised database.

**Figure 1 F1:**
[figure not shown]
Participant workflow for the alloplastic total temporomandibular joint (TMJ) replacement registry.

### Inclusion criteria

Aged 18 years and older.Patients requiring alloplastic total TMJ replacement.Informed consent obtained, that is:Ability to understand the content of the patient information/informed consent form (ICF).Willingness and ability to participate in the clinical investigation according to the research protocol.Signed and dated ethics committee (EC)/institutional review board (IRB)-approved written informed consent.

### Preoperative exclusion criteria

Patients with a recent history of substance abuse (ie, recreational drugs or alcohol) that would preclude a reliable assessment.Pregnant women or women planning to become pregnant within the study period.Participation in any other medical device or medicinal product study within the previous month that could influence the results of this study.

### Recruitment

A recruitment period of approximately 60 months is planned to enrol approximately 200 patients.

All eligible participants will be informed by a research team member about the registry’s purpose, procedures, duration, risks, benefits, alternatives to participation and data protection. Written ICF must be obtained before the TMJ replacement surgery, unless waived by the local EC/IRB or, in cases of surgery refusal, before data collection. In all cases, consent must be obtained before entering any data into the electronic case report form (eCRF).

All consented patients will be allocated a unique patient number. Each site will maintain an Identification List (IL) linking each patient’s number to their personal information. This IL is kept safe in a locked place at all times. Sites are not allowed to share the IL with any third party, except the sponsor representative, legal authorities and EC/IRB, who may have access to the IL during on-site monitoring/auditing activities.

All eligible and consented patients who underwent alloplastic total TMJ replacement will be followed up within the registry, unless their participation in the study is prematurely terminated.

Participating sites will register patients who refuse alloplastic total TMJ replacement, but these patients will not be followed up unless they choose to undergo alloplastic total TMJ replacement during the enrolment period.

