### Data collection

Patients will be followed up starting approximately 10 days after treatment and then at 3, 6, 12, 24 and 60 months. A summary of the data to be collected at each visit is shown in table 2. Unscheduled visits may occur at any time during the study in case of a medical emergency or if the investigator deems it necessary for patient care. Unscheduled visits will not be documented.

**Table 2 T2:** Study schedule

Assessment parameters	Visit 1	Visit 2	Visit 3*	Visit 4*	Visit 5*	Visit 6*	Visit 7*	Visit 8*
	Screening/preoperative	Treatment day	Postoperative 10 days (±7 days)	3 months (±30 days)	6 months (±45 days)	12 months (±60 days)	24 months (±90 days)	60 months (±90 days)
Patient information/consent	X†							
Eligibility	X†							
Baseline characteristics	X†							
Reason for refusal of TMJ replacement		X‡						
Treatment details§		X						
Pain medication	X†			X	X	X	X	X
Clinical and functional outcomes	X†		X	X	X	X	X	X
PROs	X†		X	X	X	X	X	X
Anticipated treatment or condition-related AEs	X	X	X	X	X	X	X	X
Survival			X	X	X	X	X	X
Image collection	X†		X			X	X	
Radiographical parameters¶			X			X	X	

* All postoperative FU visits within the defined time windows are calculated from the treatment day (ie, day 0).

† Assessment for patients who will undergo TMJ replacement and for patients who refused TMJ replacement.

‡ Only for patients who refused TMJ replacement.

§ For enrolled patients who underwent total TMJ replacement on one side only and have to undergo TMJ replacement on the contralateral side later during the study, details of additional surgical treatment will be collected at any time during the study.

¶ All images are taken according to local standard-of-care (routine) procedures.

AE, adverse event; FU, follow-up; PRO, patient-reported outcome; TMJ, temporomandibular joint.

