#### Adverse events (AEs)

Since this is an observational registry, only anticipated condition-related, treatment-related or implant-related AEs will be documented from the time of consent onwards. These include fixation failure (implant loosening, breakage or instability), dehiscence of incision, wound infections, neurological-related (facial nerve damage, Frey’s syndrome, sensory disturbances or altered hearing), bleeding, haematoma, swelling, injury to adjacent structures, ankylosis, malocclusion, sensitivity to material, heterotopic ossification, disarticulation, contralateral joint dysfunction, condylar resorption, graft loss, revision surgery and any other AEs that may affect the outcome of the registry.

These events are considered events of scientific interest, that is, events that can clearly be connected to the treatment(s) or the medical condition under investigation and will not require immediate reporting to the local EC/IRB unless they occur at a higher frequency and/or severity than that cited in the literature.

This registry can be considered a minimal-risk study, given that participation poses a very low risk compared with the standard-of-care (routine) procedures.

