### Statistical analysis

Since the objectives of this registry are descriptive and exploratory in nature, no formal hypothesis testing is planned, and all analyses will be exploratory. The planned sample size of 200 patients is based on the estimated number of eligible participants expected to be enrolled during the 2-year recruitment period. Eligible patients who refuse TMJ replacement will be included in the study but excluded from sample size calculations. Depending on the volume and quality of the data collected during the first 2 years, the registry may remain open thereafter, with patient FU of up to 5 years.

A detailed statistical analysis plan (SAP) will be finalised before the final analysis (ie, the analysis from which the results will be summarised in the final registry report). As the primary aim of the current registry is descriptive, patient characteristics, clinical data and outcomes recorded at standard-of-care scheduled FU assessments will be presented using descriptive summary statistics. Categorical variables will be summarised using frequency and percentage for each category. Continuous variables will be summarised using the mean, SD, median, IQR and minimum and maximum values. Analyses will also be stratified by clinically relevant categories, including treatment patterns.

Longitudinal clinical, functional and PRO data may be analysed using mixed-effects models for repeated measures, allowing inclusion of all available data and minimising the impact of missing data. Time-to-event analyses are planned, with survival status recorded at each scheduled FU. Kaplan-Meier methods will estimate survival probabilities, and multivariable Cox proportional hazards models will be used where event numbers permit.

Centre effects and geographic variability will be addressed using multilevel (hierarchical) models with patients nested within regions to account for clustering and differences in practice patterns. For time-to-event outcomes, region (or treating centre) will additionally be included as a covariate in Cox regression models when sample sizes permit. The AEs will be summarised at both patient and event levels, with rates calculated using the total population as the denominator, regardless of dropouts, with 95% CIs provided.

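### If the local waiver lets a patient consent after surgery, the rule that starts AE recording at consent leaves earlier, already resolved complications out of rates whose denominator still counts that patient

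*Protocol article*

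**What the plan says.** Five statements in the protocol article bear on this.

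- Recruitment sets the timing rule and its exception: "Written ICF must be obtained before the TMJ replacement surgery, unless waived by the local EC/IRB".
- The same paragraph then sets a floor for everyone: "In all cases, consent must be obtained before entering any data into the electronic case report form (eCRF".
- Adverse events (AEs) fixes when safety recording begins: "only anticipated condition-related, treatment-related or implant-related AEs will be documented from the time of consent onwards".
- Table 2 (Data collection) marks the row "Patient information/consent" only at Visit 1, the preoperative visit. It marks the row "Anticipated treatment or condition-related AEs" at all eight visits, including Visit 2, the treatment day.
- Statistical analysis reports AEs per patient and per event, "with rates calculated using the total population as the denominator, regardless of dropouts".

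The Inclusion criteria ask for "Signed and dated ethics committee (EC)/institutional review board (IRB)-approved written informed consent" and give no date relative to the operation.

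**The concern.** The AE window opens at consent and the denominator is everyone. These two rules fit together only if every operated patient has consented by the day of surgery. The waiver clause appears to let some patients consent later, and nothing says what then happens to AE recording for the interval already past.

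The events most exposed are those likely to arise during or soon after the operation. The article's AE list includes bleeding, haematoma, wound infection, dehiscence and facial nerve damage. If such an event comes and goes before consent, the stated rule keeps it out of the registry.

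The loss runs in one direction, towards lower complication rates. Because the waiver is local, it could also differ between centres. The Discussion names comparison of complication rates as one use of the registry, so this would reach a stated aim. No later analysis plan can recover events that sites were told not to document.

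**Working it through.** **Step 1: what the waiver can mean.**

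- *Timing.* The exception is attached to a requirement that consent come before surgery, and the next sentence still demands consent in all cases before data entry. Consent is kept and its deadline is relaxed. This is the more natural reading.
- *Written form.* The first sentence speaks of a written form and the second of consent only, so the committee might be waiving the document. Consent could then still precede surgery and no AE need be lost.

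The remaining steps apply to the timing reading only.

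**Step 2: apply the rules to a patient operated on at day 0 and consented later.**

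| Rule | Effect |
|---|---|
| Adverse events: recording starts at consent | Events that ended before consent are outside the window |
| Table 2: AEs at Visits 1 and 2 | These visits are to be documented |
| Table 2: consent only at Visit 1 | No place in the schedule for a later consent |
| Statistical analysis: whole population as denominator | The patient counts in full |

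The first two rows cannot both be followed for this patient. If the Adverse events rule prevails, the numerator is short and the denominator is not.

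**Step 3: size.** The article gives no figure to reproduce: no AE rate, no number of waivers and no power calculation. Let

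- p = true proportion of patients with an AE, taken as equal in early- and late-consented patients,
- w = share of patients consented after surgery,
- f = share of the late-consented AE patients whose events all precede consent and go unrecorded.

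Recorded rate = p × (1 − w × f), and relative understatement = w × f. All three inputs are assumptions. Only N = 200 comes from the article.

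| p | w | f | True AE patients | Recorded | Recorded rate |
|---|---|---|---|---|---|
| 20% | 0% | any | 40 | 40 | 20.0% |
| 20% | 5% | 0.5 | 40 | 39 | 19.5% |
| 20% | 10% | 0.5 | 40 | 38 | 19.0% |
| 20% | 10% | 1 | 40 | 36 | 18.0% |
| 20% | 25% | 0.5 | 40 | 35 | 17.5% |
| 20% | 25% | 1 | 40 | 30 | 15.0% |
| 5% | 10% | 1 | 10 | 9 | 4.5% |

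For example, 0.20 × (1 − 0.10 × 1) = 0.18, and 0.18 × 200 = 36.

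For scale, the Wilson 95% interval around 40/200 is 15.0% to 26.1%, so in most of these rows the shift is smaller than sampling error. It is systematic, however, and the planned 95% CIs do not allow for it.

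**The case against.** The strongest reply is that the scheduled pathway is preoperative throughout. Table 2 puts consent and eligibility at Visit 1 and AE collection on the treatment day. No postoperative consent visit exists, and the article does not say that any committee granted a waiver. The clause might concern written form only, and the full protocol, which is not shown, may explain it. This stands as a limit on size: the bias may be zero. It does not remove the defect, because the exception, the start of the AE window and the denominator are all stated here and do not fit together under the timing reading.

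Events still present at consent, such as a persisting nerve deficit, can be documented then. That also stands. It means f is below 1 in general, so the rows with f = 1 are upper bounds for their w.

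A reader might infer more than the article supports.

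- *That the waiver contradicts the Inclusion criteria.* Those criteria set no time for consent, so a patient who signs after surgery under a timing waiver still meets them. A conflict would arise only if the waiver removed written consent itself, and on that reading no AE need be lost. One clause cannot carry both complaints.
- *That baseline scores could not exist for such patients.* The rule bars eCRF entry before consent, not routine measurement. Assessments follow each centre's standard practice, so preoperative values might be entered afterwards.
- *That sites would approach mainly patients who did well.* Nothing in the article describes this, and it remains conjecture.

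**Conclusion.** The point holds conditionally. On the most natural reading of the waiver, the stated rules undercount AEs that occurred and resolved before consent, while these patients stay in the denominator. They also conflict with Table 2's AE collection on the treatment day.

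The relative understatement is w × f. It runs from 2.5% to 25% across the non-zero rows shown and is zero if no waiver was granted or if the waiver concerns form only. The result assumes that earlier AEs are not captured retrospectively, on which the article is silent, and that AE risk does not depend on consent timing. The illustrated rates rest on assumed inputs and are not estimates for this registry. The article supports neither a contradiction with the Inclusion criteria nor selection of patients by early result.

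**What to change.** 1. In Recruitment, state whether the waiver concerns the timing of consent or its written form, and whether any site holds one.
2. If it concerns timing, amend Adverse events (AEs) so that AEs in operated patients are documented from the treatment day whatever the consent date. Earlier events would be taken from the hospital record once consent is given, where the ethics committee permits. This brings the section into line with Table 2.
3. Record the consent date relative to surgery. The consent form is dated and the surgery date is already collected, so this is one derived flag.
4. Report AE rates and change from baseline with and without patients consented after surgery.

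The cost is a wording change at sites already approved, minor retrospective record review for the patients concerned, and the flag. Enrolment began in June 2021, so the flag should also be derived for patients already enrolled. If it shows that nobody was consented after surgery, the matter is closed with no effect on results.
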